## Abstract

**Background:**

Physical activity (PA) has been recommended in multiple sclerosis (MS) to maintain good physical fitness and mental health, reduce the severity of symptoms and risk of relapse, and improve quality of life. Pilates has been suggested as an ideal PA to manage physical, cognitive, and psychological symptoms of MS and a useful method to maintain and improve balance and gait.

**Objective:**

This paper presents the protocol for a study that aims to evaluate the efficacy on the physical domain (specifically balance and gait) of a home-based, self-managed PA intervention delivered through the MS-FIT exergame (HELAGLOBE Società a responsabilità limitata). In addition, measures of cognitive performance, quality of life, and well-being will be considered.

**Methods:**

This is a 2-arm, multicenter, randomized controlled trial with 3 assessment points (baseline, 12 weeks postintervention, and 6 weeks follow-up). People with MS with mild disability, low risk of falling, preserved cognitive functions, and low anxiety and depression are potential eligible participants. The experimental group (MS-FIT) will self-administer the MS-FIT exergame at home in addition to their leisure-time physical activities. MS-FIT is an internet- and Pilates-based tool that uses the Microsoft Kinect Sensor V2. Participants in the control group will only have access to their leisure-time physical activities. Participants in the MS-FIT group will train at home with MS-FIT for 12 weeks and will be required to perform the exercises for a total of 30 minutes/day for at least 3 days/week. The primary outcome is the Timed Up and Go, a test designed to assess walking. We will also administer additional tests for motor function (visual analog scale 0-10, Timed 25-Foot Walk, Ambulation Index, 2-minute walk test, Twelve Item Multiple Sclerosis Walking Scale, Nine-Hole Peg Test), cognition (Brief International Cognitive Assessment for Multiple Sclerosis), fatigue (Modified Fatigue Impact Scale), quality of life (Multiple Sclerosis Quality of Life-54), well-being (Psychological Well-Being Scales), and PA (International Physical Activity Questionnaire and Minnesota Leisure Time Physical Activity Questionnaire). Acceptance and satisfaction with the intervention received (Client Satisfaction Questionnaire and an adapted version of the Tele-healthcare Satisfaction Questionnaire – Wearable Technology) and subjective impressions of changes in performance (Patients’ Global Impression of Change) will also be assessed.

**Results:**

Recruitment for the trial started on March 16, 2022, and the first participant was randomized the same day. Data analysis and results are expected to be published in 2025.

**Conclusions:**

Pilates has proven beneficial in several neurological diseases such as MS. With this study, we will provide evidence for the use in clinical practice of a digital tool for self-administered Pilates exercises at home as a complement to rehabilitation and for the continuity of care in MS.

**Trial Registration:**

ClinicalTrials.gov NCT04011579; https://tinyurl.com/2p9n4d2t

**International Registered Report Identifier (IRRID):**

DERR1-10.2196/58026

## Introduction

Multiple sclerosis (MS) is a chronic inflammatory neurodegenerative disease with autoimmune demyelinating lesions of the central nervous system and one of the most common causes of neurological disability in young adults. Clinically, MS progressively worsens over time, leading to cumulative physical disability, cognitive deficits, and neuropsychiatric and behavioral symptoms [1]. Physical impairments lead up to 85% of people with MS to complain of ambulation difficulties after typically 10-15 years of disease, and, after 20 years, over 66% of people with MS do not retain the ability to walk [1]. Several factors, such as weakness, spasticity, cerebellar ataxia, fatigue, and impaired attention, can cause imbalance and gait disorders [2,3]. They prevent people from performing daily activities properly and regularly, with negative effects on work status and social relationships. Rehabilitation is the main option to enhance recovery from disabling symptoms such as spasticity, ataxia, sensory loss, fatigue, pain, mood, and cognitive disorders [4]. More recently, people with MS have been recommended to engage in regular physical activity (PA).

PA, including leisure-time physical activity and exercise, comprises any bodily movement produced by skeletal muscles’ contraction that results in a substantial increase in energy expenditure over resting levels [5]. Increasing PA and reducing sedentary behavior are general recommendations to improve health outcomes for all people with chronic diseases [6]. For people with MS, PA maintains good physical fitness and mental health, prevents or reduces the severity of symptoms and the risk of relapses, and improves quality of life [7-9]. Based on current evidence and experts’ opinions, recent MS guidelines recommend “at least 150 minutes/week of exercise and/or 150 minutes/week of lifestyle PA” throughout the disease course [10]. However, Klaren et al [11] report that people with MS do not engage in sufficient PA amounts, with only approximately 20% of people with MS meeting recommended levels of moderate or vigorous daily activity compared with 40% of healthy participants. Although a recent survey study reported higher rates among people with MS, only 60% of the total sample met recommendations, with the lowest rate shown in the severely disabled group [12]. Furthermore, the benefits of PA may be limited if not incorporated into a structured, personalized, and supervised program.

Various mind-body fitness modalities, such as Pilates, yoga, Tai chi, and Qigong, are widely used by people who seek to achieve physical and mental health outcomes [13,14].

Pilates has been suggested as an ideal approach to managing physical, cognitive, and psychological symptoms of MS [15] and a popular alternative method for maintaining and improving balance and gait performance [16], as in other neurological conditions [17-19]. Indeed, it is a precise and controlled form of exercise that uses the body’s stabilizing muscles and is based on the principles of concentration, control, centering, flowing movement, precision, and breathing. If followed correctly, they can improve flexibility, strength, core stability, muscle control, breathing, and posture, and increase body awareness with less ground impact and joint stress [20,21]. The research findings support the therapeutic use of Pilates in the management of MS because it is a safe, active treatment method (few adverse effects) with high adherence (low dropout rate), and it can improve important meaningful functions (eg, balance, gait, physical-functional capacities, and cognition) [22].

A possible perspective for delivering Pilates interventions could benefit significantly from the proliferation of exergames and new technologies for telerehabilitation [23]. Playing exergames is a form of whole-body physical exercise [24] that requires users to complete assigned tasks aimed at improving physical fitness and promoting an active lifestyle [25]. Furthermore, exergames have been demonstrated to be comparable with traditional therapies, may be more enjoyable and acceptable, and may improve the engagement of people with MS in PA [26]. Exergame-based telerehabilitation solutions represent an efficient alternative method to overcome barriers that prevent people with MS from accessing regular long-term rehabilitation interventions (ie, transportation and working time) and to provide effective treatments in a setting, matching the patient’s circumstances (eg, at home), priorities (eg, during lunch break), and capabilities (eg, physical impairment) [27].

Recently, MS-FIT (HELAGLOBE Società a Relazioni Limitate), a Kinect-based playable exergame implementing Pilates exercises, has been developed by an Italian network of experts in the field of MS rehabilitation for future use in research and clinics [28]. It has been customized for people with MS, allows tailoring the intervention in order to potentiate the effects of an ongoing program, and has been conceived to be developed for asynchronous telerehabilitation purposes.

The aim of this study, promoted by the Italian Multiple Sclerosis Foundation, is to test in people with MS the efficacy on the mobility domain measured with the Timed Up and Go (TUG) test of a self-managed home intervention delivered through MS-FIT in addition to leisure-time physical activities, in comparison with leisure-time physical activities alone. Measures of balance, gait, upper limb functioning, PA, cognition, quality of life (QoL), well-being, acceptability, satisfaction with use, and adherence to the intervention will also be considered. In addition, a blood sample will be collected to investigate if genetic polymorphisms that are considered potential regulators of neural plasticity could influence the response to the proposed intervention [29].

Based on previous findings [30], we expect that the intervention, in addition to leisure-time physical activities, will be associated with a primary outcome of mobility (TUG) compared with leisure-time physical activities alone that are expected to worsen due to disease progression. Similar changes between groups are expected in secondary outcomes; furthermore, based on our previous findings [28], we expect high acceptability, satisfaction-to-use, and adherence to the MS-FIT intervention.

If results are positive, MS-FIT could be proposed in combination with rehabilitation to potentiate the effect of the rehabilitation intervention and ensure continuity of care for people with MS.

## Methods

### Study Design

We are conducting a multicenter 2-arm, superiority randomized controlled trial (RCT) with 3 assessment points (baseline, T0; postintervention at 12 weeks, T1; and follow-up at 6 weeks, T2). Participants will be allocated to the intervention (MS-FIT) or control group in a 1:1 ratio by simple randomization.

Participants in the MS-FIT group will have access to the MS-FIT exergame for at-home self-administration [28] (Multimedia Appendix 1) in addition to their leisure-time physical activities. Participants in the control group will have the possibility to perform only their leisure-time physical activities. Exercise will not be allowed and rehabilitation treatments, except for speech therapy, sphincter rehabilitation, and psychological support, must be suspended. The study design is illustrated in Figure 1.

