#### Inclusion Criteria

The study includes people with a diagnosis of MS according to McDonald’s criteria [31] and aged ≥18 years; all disease courses are eligible (relapsing-remitting, primary progressive, and secondary progressive) [32]. Patients will be included if their disability level based on the Expanded Disability Status Scale (EDSS) [33] is between 2 and 4. Indeed, we expect that in people with MS with a lower EDSS, the proposed intervention might not be effective and other forms of PA based mainly on exercise should be considered. For people with MS with a higher EDSS, Pilates could be recommended as a complement but not as a replacement for rehabilitation; also, for this reason, we considered it unethical to include patients who should suspend their treatments for the aims of the study. Furthermore, asynchronous telerehabilitation tools for self-administered balance training should be proposed when the patient’s ability to maintain balance safely is preserved (eg, pregnant women will be excluded until after giving birth). In any case, we included patients with preserved balance evaluated with the Berg Balance Scale score >46 [34].

To ensure the ability to use the MS-FIT exergame, normal cognitive functioning determined by a Mini-Mental Status Examination score >24 [35] is required; a Hospital Anxiety and Depression Scale score <10 in the 2 subsets of anxiety and depression [36] could prevent a loss of adherence due to mood disorders.

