### Sample Size

The sample size was calculated by referring to the TUG change after a Pilates intervention found by Kalron et al [30] in a group of people with MS. The authors found no difference between the group receiving the Pilates intervention and the control group receiving an intervention of physical therapy. The Pilates group improved the TUG performance by about 1.8 seconds, which is clinically relevant for people with MS. Considering a variability of about 3.4 seconds, a power of 80%, a significance level (2-sided) of 5%, and a potential loss of 15% of patients at follow-up, the estimation of the necessary sample size consists of approximately 63 participants for the experimental group (a total of 126).

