### Statistical Analysis

Descriptive statistics will be used to evaluate differences between the 2 groups of participants. The study hypotheses will be tested using an intention-to-treat analysis, where all consenting patients who were randomized during the accrual period will be included in the analysis.

Continuous data will be summarized using count, mean, median, SD, and IQRs, whereas categorical measures will be described using frequencies. The assumption of normality will be tested with the Shapiro-Wilk test. Pre-post effects within groups will be investigated using the paired *t* test or the Wilcoxon matched-pairs signed-rank test. Between-group proportions will be compared by chi-square or Fisher exact test, while between-group comparisons for continuous variables will be done using either the unpaired 2-sided *t* test or the 2-sided Wilcoxon 2-sample test for nonnormal data. Correlations will be computed using Pearson or Spearman coefficients.

The primary analysis will be performed by comparing mean changes from T0 to T1 in the primary and secondary study outcomes. In particular, the MS-FIT group will be compared with the control group with analyses of covariance. The model includes change as the dependent variable, with the intervention group as the main effect and baseline and number of sessions as additional covariates. Finally, generalized estimating equation models will be performed to assess the persistence of the intervention effect; here the mean effect of the intervention at the time points T0, T1, and T2 on all outcomes, adjusted for the baseline value, will be evaluated between the 2 groups.

Differences in the outcome measures between subgroups defined by different polymorphisms will be analyzed using the analysis of variance or the Kruskal-Wallis test, as appropriate.

Statistical analysis will be performed using STATISTICA 7.1 software (StatSoft GmbH). Significance will be recognized for *P*<.05.

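### Baseline EDSS and centre are left out of the primary model of a multicentre trial with simple randomisation; prespecifying them would be a cheap, modest gain in precision and robustness, not the repair of an error

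*Protocol article*

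**What the plan says.** Study Design describes a two-arm multicentre superiority trial and fixes the allocation: "Participants will be allocated to the intervention (MS-FIT) or control group in a 1:1 ratio by simple randomization". No stratification factor, block or minimisation is mentioned.

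Statistical Analysis then writes out the primary model. The dependent variable is the T0 to T1 change, analysed by ANCOVA "with the intervention group as the main effect and baseline and number of sessions as additional covariates". The later generalized estimating equation model is described as "adjusted for the baseline value, will be evaluated between the 2 groups". I read baseline in both places as the baseline value of the outcome, that is, T0 TUG for the primary outcome. Neither model names centre or EDSS.

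Both variables are already in hand. Under Inclusion Criteria, patients enter if their "disability level based on the Expanded Disability Status Scale (EDSS) [33] is between 2 and 4", and the section on recruitment, enrollment and randomization has eligibility checked at a screening visit before allocation. The centre is known for every patient.

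**The concern.** Simple randomisation balances nothing by design except in expectation. In a trial of 126 patients spread over several centres, the arms can differ by chance in baseline disability and in their mix of centres. The article itself treats EDSS as relevant to response: Inclusion Criteria explains the lower limit by an expectation that the intervention may not work at lower EDSS. All 126 patients are enrolled (Results), so allocation can no longer be changed, and the model is the only place left to deal with such imbalance. The covariates have to be named before the data are analysed, because a list chosen afterwards carries less weight.

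The covariate list is stated in the text, so this concerns what the article fixes, not a detail left to an analysis plan. At stake are some precision and some robustness of the primary estimate. Validity is not at stake.

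**Working it through.** **Inputs from the article.** Sample Size: "The Pilates group improved the TUG performance by about 1.8 seconds"; "Considering a variability of about 3.4 seconds"; 80% power; two-sided 5%; 15% loss; 63 per arm, 126 in total. Results: 108 patients with a T1 visit, or 54 per arm if evenly split.

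**Assumptions, not in the text shown.** The share R of residual variance explained by EDSS and centre beyond baseline TUG, taken from 0 to 10% (15% in one simulated setting); and 3, 5 or 8 centres.

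**The plan's own figure.** n per arm = 2 × (1.960 + 0.842)² × 3.4² / 1.8² = 56.0, so 57. Dividing by 0.85 gives 67.1, so 68; multiplying by 1.15 gives 65.6, so 66. The stated 63 is a little lower, and 63 × 0.85 = 53.6, about 54 per arm. This point does not depend on that gap.

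**Chance imbalance, exact binomial or normal**
- Overall split of 71:55 or worse among 126: probability 18%. Efficiency relative to 63:63 is 71 × 55 / 63² = 0.984, a loss of 1.6%.
- A hypothetical centre of 20 patients: 14:6 or worse has probability 11.5%.
- Any one baseline factor: the standardised difference between arms has SD √(4/126) = 0.178, so a difference beyond 0.25 SD has probability about 16%. If that factor explains 5% of residual variance, an imbalance of 0.25 SD shifts the estimate by 0.25 × √0.05 × 3.4 = 0.19 s, against the planned 1.8 s.

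**Power before charging for extra terms.** SE = 3.4 × √(1 − R) × √(2/54), with noncentral t power for 1.8 s:

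| R | Power |
|---|---|
| 0 | 77.8% |
| 2% | 78.6% |
| 5% | 79.9% |
| 10% | 81.9% |

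**Charge for k extra terms.** With 108 patients and three terms already counted (intercept, group, baseline), the variance factor is approximately (1 − R) × (1 + k/(105 − k)).
- EDSS alone, k = 1, R = 0: 1 + 1/104 = 1.0096, so the SE rises by 0.5%.
- EDSS plus eight fixed centres, k = 8, R = 0: 1 + 8/97 = 1.0825, so the SE rises by 4.0%.
- Break-even is at R = k/105: 1.0% for EDSS alone; 2.9%, 4.8% and 7.6% for EDSS plus 3, 5 and 8 fixed centres.
- Net power for EDSS alone: 79.5% at R = 5% and 81.6% at R = 10%.
- Net power for EDSS plus 3, 5 or 8 fixed centres at R = 10%: 80.8%, 80.0% and 78.8%.

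**Simulation check.** 2,500 runs per setting, 108 patients, simple randomisation, baseline TUG always in the model, centres as fixed effects. Power for 1.8 s, without → with EDSS and centre:

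| Variance from centre + EDSS | 3 centres | 5 centres | 8 centres |
|---|---|---|---|
| 0 + 0 | 76.9 → 75.9% | 76.4 → 74.3% | 78.1 → 75.0% |
| 2% + 2% | 78.6 → 78.8% | 77.7 → 77.2% | 78.2 → 76.2% |
| 5% + 5% | 77.5 → 80.8% | 78.1 → 80.4% | 77.7 → 78.3% |
| 10% + 5% | 78.1 → 82.4% | 78.3 → 80.8% | 78.4 → 81.1% |

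Type I error under no effect lay between 4.2% and 6.0% over all settings and both models, within about two simulation errors of 5%.

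**The case against.** The strongest case against is that nothing here is wrong. With simple randomisation there are no stratification factors that the model must carry, and ANCOVA without centre or EDSS is valid. That stands, and it limits the point to a recommendation. Baseline TUG is already a covariate and EDSS is confined to a narrow range, so little further explained variance can be presumed. That also stands.

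Several stronger readings are tempting, and the article does not support them.
- A reader might infer that adjustment is free. It is not: with weakly prognostic covariates and several fixed centres, power falls.
- A reader might infer that the gain would make good the small gap to 80% power. That rests on an explained variance that the article does not give. The 77.8% starting point is itself approximate, since Sample Size does not say whether 3.4 s is the SD of change or of raw TUG.
- A reader might infer that differences in hand timing between sites make centre a source of variance. Primary Outcome says only that the participant is timed, and a constant site difference would largely cancel in a change score. Training by the study manager before the intervention concerns the use of MS-FIT, so a trainer effect would act mainly as a centre-by-treatment difference, which a centre main effect does not remove.
- A reader might infer that adjustment repairs unequal arm sizes. It does not, and a 71:55 split costs only 1.6% in any case.

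What remains is that EDSS is a baseline measure already collected, costs about 0.5% in SE if useless, and breaks even at about 1% of residual variance.

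**Conclusion.** The point holds as a low-cost improvement. The stated primary model omits two variables known before randomisation, in a design that does nothing else to balance them. The case is clearest for EDSS, where the possible loss is negligible and the gain is roughly 2 to 4 points of power if it explains 5 to 10% of residual variance. For centre the balance depends on how many centres there are and how they are handled: fixed effects for many small centres can cost more than they return. All the gains rest on assumed explained variance and centre numbers, with 1.8 s, 3.4 s and 54 per arm taken from the article. Adding these covariates does not touch a separate matter in the same sentence, the use of number of sessions as a covariate.

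**What to change.** Before the data are analysed, prespecify baseline EDSS as a covariate beside baseline TUG in the model for T0 to T1 TUG change, and carry the same covariate into the repeated-measures model. Account for centre by a random intercept, or by a fixed factor with small centres pooled under a rule written down in advance. A generalized estimating equation model has no random intercept, so the pooled factor is the option there. Report the model without these terms as a sensitivity analysis.

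The cost is a few sentences in the analysis plan, a few degrees of freedom and, if the covariates prove not to be prognostic, the slightly larger SE shown above. No new data are needed, and the allocation already made is unaffected.

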**Figure 1 figure1:**
[figure not shown]
Study design.

### Recruitment, Enrollment, and Randomization

People with MS along with mild disability, low risk of falling, preserved cognitive functions, and low anxiety and depression as reported in medical records are potential eligible participants. They will be contacted by telephone by the study manager of the related center (Multimedia Appendix 1), who will explain the study process in detail to ensure that patients understand the entire clinical trial; they will receive detailed information, including the purpose, procedures, follow-up content, data storage, benefits, and risks of the study, and will be given adequate time to consider participation. They will be informed that for the entire period of participation in the study, only leisure-time physical activities will be allowed, but not exercise and rehabilitation. They will also be informed verbally that their participation is voluntary and that they can withdraw their consent at any time without giving reasons and without depriving themselves of any treatment and care or other disadvantages.

Patients who agree to participate will be scheduled for a screening visit with a therapist (Multimedia Appendix 1). First, they will be asked to sign the written informed consent (Multimedia Appendix 2) after carefully reading and understanding the information about the study procedures and data security measures (including information on how to contact the study team in case of questions) provided to them. This approach is compliant with the General Data Protection Regulation and has been approved by the ethics committees.

After consent, recruited patients will proceed to the screening evaluation, where inclusion and exclusion criteria are assessed, and they will immediately receive feedback on whether or not they can participate in the study. Enrolled patients will be randomized by the study manager through the electronic case record form (eCRF) (Multimedia Appendix 1) into one of the 2 groups (ie, MS-FIT and control) and informed of the result of the assignment.

